# Impact of Remote Titration Combined With Telemonitoring on the Optimization of Guideline-Directed Medical Therapy for Patients With Heart Failure: Protocol for a Randomized Controlled Trial

**DOI:** 10.2196/19705

**Published:** 2020-10-13

**Keywords:** telemonitoring, telemedicine, remote titration, mHealth, heart failure

## Abstract

**Background:**

Guideline-directed medical therapy (GDMT), optimized to maximum tolerated doses, has been shown to improve clinical outcomes in patients with heart failure (HF). Timely use and optimization of GDMT can improve HF symptoms, reduce the burden of hospitalization, and increase survival rates, whereas GDMT deferral may worsen the progression of HF, decrease survival rates, and predispose patients to poor outcomes. However, studies indicate that GDMT remains underused, with less than 25% of patients receiving target doses in clinical practice. Telemonitoring is a potential component in the management of HF that can provide reliable and real-time physiological data for clinical decision support and facilitate remote titration of medication.

**Objective:**

The primary objective of this study is to evaluate the impact of remote titration facilitated by telemonitoring on health care outcomes, with a primary outcome measure being the proportion of patients achieving target doses. The secondary objective is to identify the barriers and facilitators that can affect the implementation and effectiveness of the intervention.

**Methods:**

A mixed methods study of a smartphone-based telemonitoring system is being conducted at the Peter Munk Cardiac Centre (PMCC), University Health Network, Toronto. The study is based on an effectiveness-implementation hybrid design and incorporates process evaluations alongside the assessment of clinical outcomes. The effectiveness research component is assessed by a two-arm randomized controlled trial (RCT) aiming to enroll 108 patients. The RCT compares a remote titration strategy that uses data from a smartphone-based telemonitoring system with a standard titration program consisting of in-office visits. The implementation research component consists of a qualitative study based on semistructured interviews with a purposive sample of clinicians and patients.

**Results:**

Patient recruitment began in January 2019 at PMCC, with a total of 76 participants recruited by February 24, 2020 (39 in the intervention group and 37 in the control group). The final analysis is expected to be completed by the winter of 2021.

**Conclusions:**

This study will be among the first to provide evidence on the implementation of remote titration facilitated by telemonitoring and its impact on patient health outcomes. The successful use of telemonitoring for this purpose has the potential to alter the existing approach to titration of HF medication and support the development of a care delivery model that combines clinic visits with virtual follow-ups.

**Trial Registration:**

ClinicalTrials.gov NCT04205513; https://clinicaltrials.gov/ct2/show/NCT04205513

**International Registered Report Identifier (IRRID):**

DERR1-10.2196/19705

## Introduction

### Background

Heart failure (HF) is a global public health problem affecting an estimated 26 million worldwide [1]. Researchers estimate that more than 1 million people in Canada are living with HF, about 50,000 new cases are diagnosed each year, and HF costs the Canadian health care system Can $2.8 (US $2.12) billion annually [2,3]. The rapidly aging population in developed countries and improved prognosis of HF are contributing to the increasing prevalence of people with HF. However, although HF prognosis has improved, the long-term mortality rates for the condition remain high. Approximately 1 in 3 patients admitted to the hospital with HF still die within a year and approximately 1 in 2 die within 5 years [4].

In addition, HF accounts for 1% to 2% of direct health care expenditure in developed countries [5] and the cost to our health care system is expected to grow with the aging of the population and rising prevalence of HF. In Canada alone, studies found that in 2013, HF hospitalizations accounted for Can $482 (US $364.34) million in spending. By 2030, the amount is estimated to increase to Can $722 (US $545.75) million [6].

Over the past few years, significant progress has been made in pharmacological therapies for HF. Guideline-directed medical therapy (GDMT) for patients with HF, comprising angiotensin-converting enzyme inhibitors (ACEIs), angiotensin receptor blockers (ARBs), angiotensin receptor-neprilysin inhibitors (ARNIs), beta blockers (BBLs), and mineralocorticoid receptor antagonists (MRAs), has been shown through randomized controlled trials (RCTs) to improve symptoms, reduce the burden of hospitalization, and increase survival rates [7]. Conversely, a meta-analysis conducted in 2017 by Zaman et al [8] showed that a 1-year deferral of treatment could reduce the 1-year survival rate from 90% (if treated) to 78%. GDMT deferral may also worsen HF progression and predispose patients to worse outcomes [9]. Clinical guidelines recommend up-titrating these treatments to maximum tolerated doses [10]. However, these successes have not fully translated into clinical practice, as studies and registries consistently report that evidence-based pharmacotherapies for HF are severely underutilized [11,12].

Barriers including patient-related factors such as time constraints and financial limitations, physician-related issues such as knowledge of drug therapy optimization, and institution-related logistical issues surrounding clinic visits often complicate the titration process [13]. In addition, the dynamic nature of HF presents challenges in patient care and management, with patients receiving care in primary, acute, and community care settings and with frequent transitions between care providers [14]. These frequent transitions of care across multiple providers and multiple settings are poorly coordinated and often exacerbate the difficulty of medication titration [15]. All these factors impede timely optimization of vital therapy for patients with HF, which is particularly detrimental because delays in therapy can lead to significant disease progression that may have been preventable [9].

Telemonitoring is a potential component in the management of HF that can provide reliable and real-time physiological data for clinical decision support, alerting, and patient self-management. Telemonitoring enables patients to track vital signs and symptoms and receive automated instruction and clinical intervention during *teachable moments* (ie, clear actions are provided when the context is most appropriate). The acquired physiological and symptom data can also help inform clinical decisions by health care providers, such as remote titration of medication [16]. 

### Objectives

This study aims to explore how the combination of remote titration and telemonitoring affects GDMT optimization compared with standard of care. The study takes a dual focus in assessing both the clinical effectiveness and implementation of the intervention. The primary objective of this study is to evaluate the impact of remote titration facilitated by telemonitoring on health care outcomes, including the proportion of patients achieving target doses, time to dose optimization, and patient health outcomes. The secondary objective of this study is to obtain a deeper understanding of the experiences of clinicians and patients with HF participating in the remote titration program to identify factors that affect the implementation of the intervention.

## Methods

### Study Design Overview

The study is based on a type 1 effectiveness-implementation hybrid design. In this type of study, the primary aim is to determine effectiveness, and the secondary aim is to explore the implementation of the innovation [17]. This is a mixed methods study with 108 patients with HF, consisting of an RCT and a qualitative study. The RCT predominantly addresses the effectiveness component while providing supporting data for the implementation component of the research. The qualitative study predominantly addresses the implementation component while providing supporting data for the effectiveness component. In addition, the study included an internal pilot [18] that aimed to identify the most suitable primary outcome measure and obtain more accurate data to inform an appropriate sample size calculation.

This study has received approval from the research ethics boards of the University of Toronto (research ethics board number 00036655) and the research ethics boards at the University Health Network (UHN; research ethics board number 18-5351), where patients are recruited and patient data are stored. The study has also been registered at ClinicalTrials.gov (NCT04205513).

### Sample Size Calculation

One of the main outcome measures of this study, the number of visits required to complete titration, was used to calculate the initial sample size based on data obtained from the existing literature. Assuming biweekly titration over a period of 3 to 6 months (ie, 9±3 visits in total for the control group) as recommended by HF guidelines [10,19], a reduction of at least 35% in the number of visits for the intervention group, 80% power, and α=.05 (two-sided), the sample size per group was calculated to be 16. Furthermore, assuming that as much as 30% of the patients may be lost to follow-up or cannot be titrated, the sample size per group became 21. Hence, 42 patients were enrolled for the internal pilot portion of the study.

Data from the internal pilot and the literature were combined to perform the final sample size calculation. It was determined that the initially selected primary outcome measure of the number of visits required to achieve titration was not appropriate because clinic visits were strongly affected by external factors unrelated to the intervention. Many patients in the control group attended very sporadic clinic visits, which resulted in a slow and unpredictable titration process. Therefore, the new calculation was based on an alternative primary outcome measure, which was the proportion of patients achieving target doses. In the pilot cohort, 18 of 21 patients (86%) in the intervention group and 10 of 21 patients (48%) in the control group completed titration within 6 months of enrollment. According to an expert panel conducted by the Canadian Cardiovascular Society, most physicians (55%) believed that the entire triple therapy titration to maximum tolerated or target doses should be completed within 4 months, 93% believed that this should be done within 6 months, and all respondents agreed that every titration would not necessarily require a face-to-face visit [19]. The titration completion rates reported in the literature vary, and the timelines are not always clear. However, multiple studies reported that 17% to 43% of patients achieve target doses within 3 to 6 months [12,20,21].

In light of the varying ranges provided by available data and to ensure that the sample size of the full study would be sufficient to detect statistical significance, a higher completion rate among those available was used for the control group, and a slightly more conservative completion rate was used for the intervention group. Therefore, rates of 45% and 75% were used for the control and intervention groups, respectively. The calculation assumed a power of 80%. An alpha of .025 (two-sided) was used, instead of .05, to account for the single interim analysis conducted. On the basis of this, the sample size per group was calculated to be 49. Furthermore, assuming that up to 10% of the patients may be lost to follow-up or cannot be titrated (based on the observed attrition rate in the internal pilot), the sample size per group was calculated to be 54. Hence, the overall sample size of the study is 108 patients.

### Medly Telemonitoring System

Medly, a mobile phone–based telemonitoring program for patients with HF was launched at UHN in 2016. This program is integrated into the Ted Rogers Centre of Excellence in Heart Function at the Peter Munk Cardiac Centre (PMCC) as part of the standard of care.

Medly enables patients with HF to take clinically relevant physiological measurements with wireless home medical devices in addition to answering symptom questions through the mobile phone app. The measurements are automatically and wirelessly transmitted to the mobile phone and then to a data server. Specifically, patients monitor daily weight, blood pressure, heart rate, and symptoms, and some patients monitor their activity as determined by their cardiologist. Daily reports are typically completed every morning (patients receive an automated reminder call if the measurements are not performed by 10 AM), and patients are instructed to record their blood pressure and symptoms if they feel unwell. Automated self-care instructions that have been carefully developed with health care specialists are sent to the patient in accordance with a rule-based algorithm that analyzes their measurements and reported symptoms [22]. If there are signs indicating deterioration in their status, an email alert is sent to a clinician at the Heart Function Clinic. Clinicians can also view alerts and the patient’s telemonitoring data through a secure web portal. The data are monitored by a dedicated Medly nurse coordinator during working hours and an assigned clinician after hours and on weekends. Medly has a demonstrated positive impact on patient outcomes and patient experience. An RCT conducted with Medly at the Heart Function Clinic and an evaluation of the Medly Program as part of the standard of care found improvements in patient health outcomes and high patient and health care provider satisfaction. Adherence to daily monitoring was high, and the cardiologists and nurse practitioners indicated that Medly improved information transfer from their patients because they received real-time patient information and alerts that supported clinical decision making [23,24].

Therefore, Medly was chosen as the system to support the titration of HF medication for this study. Specifically, the intent was for Medly to be used to provide frequent and real-time data to support clinical decisions on the optimal modification of patients’ medications remotely.

### Study Protocol

#### Participant Enrollment and Randomization

##### RCT

Study participants are recruited from the PMCC Heart Function Clinic. Eligible participants are first identified by the cardiologist. During their usual visit to the Heart Function Clinic, all patients who meet the study’s inclusion and exclusion criteria (listed in Textboxes 1 and 2, respectively), are told about the study and asked by a member of their circle of care if they are willing to speak to the nurse coordinator regarding participation. Patients who agree meet with the coordinator immediately after their visit with the cardiologist, and a written informed consent is obtained from each patient. Patients are then randomized 1:1 into control and intervention groups. A web-based computer-generated randomization tool is used to perform block randomization in blocks of 4. The generated sequence is used to create randomization envelopes, and the nurse coordinator is provided with randomly generated treatment allocations within sealed opaque envelopes. Following enrollment, the envelopes are used to determine if the patient is in the intervention or control group. Cardiologists are notified into which group their patients are randomized.

Patient inclusion criteria.Able to provide informed consent to participate in the program18 years or olderDiagnosed as having heart failure (HF) and followed up by a cardiologist at the Peter Munk Cardiac Centre Heart Function Clinic, who has the primary responsibility for management of the patient’s HFNew York Heart Association Classes I to IIIStable HF defined as no hospitalization within 1 monthPatient is not yet at target doses of guideline-directed medical therapy (angiotensin-converting-enzyme inhibitor, and/or angiotensin receptor blocker, and/or beta blocker, and/or angiotensin receptor-neprilysin inhibitors, and/or mineralocorticoid receptor antagonist at suboptimal doses), and hence qualifies for up-titrationPatient or their informal caregiver speaks and reads English adequately to participate in the program and understand the alerts or prompts in the Medly applicationAbility to comply with using Medly (eg, able to stand on the weight scale, able to answer symptom questions)

Patient exclusion criteria.Active acutely decompensated heart failureAlready on target doses of guideline-directed medical therapyInability to titrate medications due to adverse events including:History of angioedemaUncontrolled hypertensionHypotension preventing up-titrationHeart rate at rest <56 beats per minuteCongenital heart diseasePrevious heart transplant or currently awaiting heart transplantAcute coronary syndrome; stroke; transient ischemic attack; cardiac, carotid, or other major cardiovascular surgery; percutaneous coronary intervention; or carotid angioplasty within 6 weeks before randomizationObstructive or restrictive cardiomyopathySecond- or third-degree atrioventricular block without a pacemakerPresence of hemodynamically significant mitral and/or aortic valve disease, except mitral regurgitationPresence of other hemodynamically significant obstructive lesions of the left ventricular outflow tract, including aortic and subaortic stenosis, which are not controlled with suitable treatmentEvidence of hepatic impairment defined as alanine aminotransferase or aspartate aminotransferase value >3-fold the upper normal limit. Estimated glomerular filtration rate (eGFR) <30 mL/min/1.73 m^2^ at randomization or >35% decline in eGFR between visitsKnown stenosis of both renal arteriesHyper- or hypothyroidism not controlled by treatmentHyperkalemia >5.5 mmol/L at randomizationHyponatremia <130 mmol/L at randomizationHistory of severe asthma or pulmonary diseasePresence of any other disease, which in the clinician’s opinion would exclude the patient from the study or with a life expectancy of <1 year

##### Qualitative Study

Patients randomized into the intervention group will be invited to participate in individual interviews intended to assess their experience and perception of the program upon titration completion. Maximum variation sampling [25] will be used to interview a varied selection of people. Participants will be purposively selected to represent a range of experiences with the intervention and include men and women, old and young, and patients who reside at varying distances from the clinic.

All health care providers and study staff from the Heart Function Clinic who participate in the remote titration program during the RCT will also be invited to participate in semistructured interviews through an email. Written informed consent will be obtained before the start of any interview.

Semistructured interview guides will be developed to explore the participants’ views on various aspects of the remote titration program. To ensure that the information generated is based on the participants’ unique perspectives, questions will not follow any specific constructs. During the interview, participants will be asked open-ended questions to ascertain their comfort with the intervention and its delivery, any concerns or difficulties they may have had with respect to the intervention, and whether it met their goals or expectations. Follow-up questions will explore topics raised by participants.

#### Intervention Versus Control Groups

The recommended therapeutic approach for patients with HF and reduced left ventricular ejection fraction (LVEF<40%) consists of triple therapy with either an ACEI or ARB or ARNI, BBL, and MRA, titrated to target doses [10]. However, these doses are not often achieved in clinical practice [7]. Patients identified as receiving suboptimal doses of HF medications are enrolled and randomized at a ratio of 1:1 to 1 of 2 treatment groups:

Control group—standard titration management strategy consisting of regular in-office visits.Intervention group—remote titration management strategy consisting of telephone contacts facilitated by data from the Medly system and in-office visits as deemed necessary by the patient’s care team.

Both groups are titrated in accordance with the recommendations of the HF management guidelines. Participants in the intervention group, as per Medly standard of care, are asked to take daily weight and blood pressure readings and answer questions on symptoms. Patients are also provided with requisitions for blood work to be performed at local laboratories when requested. Titration checkpoints are scheduled biweekly unless specified otherwise by cardiologists. Patients are contacted by phone, and medication changes are performed during these calls based on data obtained through Medly and the latest blood work. Patients in the intervention group still visit the hospital for follow-ups at their cardiologist’s discretion and to perform echocardiograms, electrocardiograms (ECGs), and cardiopulmonary exercise testing (CPET).

Participants in the control group attend regular visits and are provided with the current standard of care. As the Medly system is integrated into the PMCC Heart Function Clinic as part of the standard of care, patients in the control group are also monitored through Medly. However, no remote titrations occur, and medication changes are performed during clinic visits. At the clinic visit, patients have their measurements taken, such as their blood pressure, weight, and heart rate. The clinicians inquire about their symptoms, diet, exercise, and adherence to medication. Blood tests, echocardiograms, ECGs, and CPETs are performed as required. Medication changes are performed based on the data collected through these assessments.

The titration process is terminated when patients reach target doses or maximum tolerated doses. A follow-up clinic appointment is scheduled within 3 months of titration completion, as per the standard of care. Throughout this process, the importance of patients’ adherence to program requirements in terms of daily measurements and symptom reporting is emphasized and strictly monitored to ensure prompt identification of potential changes in their condition.

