#### Data Collection

##### RCT

The primary outcome measures will be the proportion of patients who achieve target doses and the time to dose optimization. Additional measures will include patient health outcomes (including, but not limited to, New York Heart Association [NYHA] class, LVEF, and brain natriuretic peptide [BNP] levels), the number of visits and/or calls required to achieve target doses, and health care resource utilization.

Information will be obtained by reviewing the patients’ electronic patient record (EPR) charts and Medly data and documentation throughout the study by the study coordinator. Baseline and poststudy medications and dosages for each patient and baseline and poststudy clinical measures, including NYHA class, LVEF, and BNP levels, will be determined through manual EPR chart reviews. Health care utilization will primarily be determined through EPR chart reviews. However, this information will be supplemented through patient self-reporting to account for situations in which patients use services outside of UHN. Data regarding the titration process, such as the number of visits and/or phone calls performed, actions undertaken, and any adverse events that occurred throughout the study, will be documented by the study coordinator. The number of visits, phone calls, and total contact points will be recorded in detail for each group to determine the impact of remote titration on the GDMT optimization process.

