##### Qualitative Study

The qualitative study will aim to identify the barriers to and facilitators for implementation. Semistructured one-on-one interviews will be conducted with participants to explore their views on various aspects of the remote titration program. Patients randomized into the intervention group will be interviewed in a quiet and private space within the clinic or over the telephone. Interviews are expected to last between 15 and 30 min. Additional interviews will be conducted until data saturation is reached and the interviewer determines that no new pertinent information is being collected. Health care providers from the Heart Function Clinic who participate in the remote titration program will also be interviewed. The individual interviews are expected to last between 20 and 45 min and will be conducted in the clinician’s office or over the telephone. All interviews will be audio-recorded and transcribed for subsequent analysis.

The schedule for data acquisition is shown in Table 1.

**Table 1 table1:** Schedule for data acquisition indicated by checkmarks at the specified time point.

Data collected		Baseline	Interim analysis	Titration completion	3-month follow-up
Demographics		✓	N/A^a^	N/A	N/A

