#### Data Analysis

##### RCT

Descriptive, parametric, and nonparametric statistics will be performed. Statistical analyses will be selected in accordance with the data under review and the required level of comparison: McNemar tests will be performed on binary baseline and poststudy data, whereas chi-square tests will be performed to compare binary poststudy data between the intervention group and the control group; paired Student *t* tests and Wilcoxon signed-rank tests will be performed on baseline and poststudy data for normally and not normally distributed data, respectively. Independent Student *t* tests and Mann-Whitney tests will be performed to compare poststudy data between the intervention group and the control group for normally and not normally distributed data, respectively.

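### After baseline, LVEF, BNP and NYHA class are timed from titration completion, itself an outcome expected to differ by arm, so the poststudy comparison can mix different follow-up times or differently selected patients

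*Protocol article*

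**What the plan says.** Under Intervention Versus Control Groups, the protocol article gives the rule that ends titration: "The titration process is terminated when patients reach target doses or maximum tolerated doses". It sets no time limit from randomization. The next sentence places the follow-up: "A follow-up clinic appointment is scheduled within 3 months of titration completion, as per the standard of care".

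Table 1 has four columns: baseline, interim analysis, titration completion and 3-month follow-up. BNP and NYHA class are ticked in all four. LVEF is ticked only at baseline and at the 3-month follow-up. No post-baseline column is a fixed time from randomization.

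The values to be analysed are described under Data Collection, RCT: "baseline and poststudy clinical measures, including NYHA class, LVEF, and BNP levels, will be determined through manual EPR chart reviews". Data Analysis, RCT then states: "Independent Student *t* tests and Mann-Whitney tests will be performed to compare poststudy data between the intervention group and the control group". Neither section dates the poststudy value. Data Collection, RCT also says: "The primary outcome measures will be the proportion of patients who achieve target doses and the time to dose optimization". For the control arm, Intervention Versus Control Groups adds: "Blood tests, echocardiograms, ECGs, and CPETs are performed as required".

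**The concern.** Whether and when a patient reaches the last two columns of Table 1 depends on completing titration. That happens after randomization, and the trial is designed to show that it differs by arm. A test of poststudy LVEF, BNP or NYHA class built on this schedule is exposed to the effect under study in one of two ways:

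- Slow patients are eventually measured. The arms are then compared at different times since randomization, in a condition that changes with time.
- Slow patients are not measured. The test then compares a larger, less selected group of intervention completers with a smaller, more selected group of control completers.

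In neither case does the comparison cleanly estimate the effect of the randomized strategy on patient health. Data Collection lists these measures as additional, but the Objectives section puts patient health outcomes within the primary objective, so the comparison should be interpretable.

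**Working it through.** **Inputs (Sample Size Calculation).** Pilot completion within 6 months of enrollment: 18/21 = 86% intervention, 10/21 = 48% control. Design rates: 75% and 45%. Planned size: 49 per group, 54 with attrition, 108 in total.

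**The plan's own figure.** For 45% vs 75%, two-sided alpha 0.025 and 80% power, the arcsine formula gives 48.9, so 49 per group; the pooled formula gives 50. Then 49 × 1.1 = 53.9, so 54. The sample size reproduces closely and is not in dispute.

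**Scenario A: everyone is eventually measured.** Assume a constant completion rate λ = −ln(1 − p)/6 per month, with p the 6-month completion proportion. Median completion is ln 2/λ. Place the follow-up 3 months later, the latest point that the text allows.

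| Rates | Arm | λ | Median completion (months) | Follow-up (months) |
|---|---|---|---|---|
| Pilot | Intervention | 0.324 | 2.1 | 5.1 |
| Pilot | Control | 0.108 | 6.4 | 9.4 |
| Design | Intervention | 0.231 | 3.0 | 6.0 |
| Design | Control | 0.0996 | 7.0 | 10.0 |

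The median gap is 4.3 months (pilot) or 4.0 months (design). It stays the same if the visit falls earlier than 3 months by the same amount in both arms. No patient is lost in this scenario, so there is no selection.

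**Scenario B: only patients complete by 6 months are measured.**

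- Pilot rates: 54 × 18/21 = 46.3 vs 54 × 10/21 = 25.7.
- Design rates: 54 × 0.75 = 40.5 vs 54 × 0.45 = 24.3.
- Standard error relative to all 108 patients: √(1/46.3 + 1/25.7)/√(2/54) = 1.28 (pilot) and √(1/40.5 + 1/24.3)/√(2/54) = 1.33 (design).
- Mean completion time among these completers, 1/λ − 6(1 − p)/p: 2.1 vs 2.7 months (pilot) and 2.3 vs 2.7 months (design). The timing gap nearly disappears, and selection is what remains.

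**What selection could do in Scenario B (illustration).** Assume no true effect, and that everyone who would complete under control would also complete under remote titration. The share of intervention completers who would not have completed under control is (18 − 10)/18 = 44% (pilot) or (0.75 − 0.45)/0.75 = 40% (design). If these patients differ from the other completers by 0.25 to 0.75 SD (assumed), the contrast shifts by 0.40 × 0.25 = 0.10 SD to 0.44 × 0.75 = 0.33 SD. The article gives neither the size nor the sign of that difference.

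**The interim column.** This is one study-level look, not a fixed time for each patient. If it is the 42-patient pilot look (an inference), it gives no value for the other 108 − 42 = 66 patients. It never covers LVEF.

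**The case against.** The strongest reply is that a patient who is not complete at 6 months may still be measured. Titration can also end at the maximum tolerated dose and has no deadline. The article puts patients lost or not titratable at up to 10%, based on pilot attrition, while 14 of 42 pilot patients (33%) were incomplete at 6 months. Most of those were probably still being titrated (an inference). If 5% vs 15% were never measured (assumed), 51.3 vs 45.9 patients would contribute and the standard error would rise by only about 6%. This stands, and it makes Scenario B an upper bound on loss. It also moves the problem to Scenario A, where slow patients are measured late.

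Three further points stand:

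- A reader might infer that non-completers have no scheduled value at all. That is wrong for BNP and NYHA class, which have the interim tick; only LVEF has no other post-baseline assessment.
- A reader might infer that clinically prompted testing is a control-arm problem. Intervention patients also have blood work on request and visits at the cardiologist's discretion.
- The analysed value comes from chart review and is not expressly limited to completers, so a comparison of completers only is a possible reading and not a stated rule.

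It can also be said that an article leaves visit windows to the full protocol or analysis plan. That answers a missing window. It does not answer a schedule which, as printed, ties these measurements to an arm-dependent event.

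**Conclusion.** The point holds as a weakness of the printed schedule. Apart from one interim look at BNP and NYHA class, post-baseline clinical values hang on titration completion, and the poststudy tests can be distorted by timing or by selection. Under a constant completion rate, the timing version is a median of about 5 vs 9 months (pilot) or 6 vs 10 months (design). The selection version is about 46 vs 26 (pilot) or 40 vs 24 (design) patients of 54 per arm. The two must not be added, because the first assumes that everyone completes and the second that slow patients are never measured.

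A reader might go further and conclude that the comparison is biased by a known amount, or against the intervention. The documents do not support this. No link between ease of titration and change in LVEF, BNP or NYHA class is given. Sample Size Calculation also attributes slow control titration to sporadic visits and to external factors, so control completers are not clearly the easiest patients to titrate. The supported wording is that the comparison can be biased. The primary proportion reaching target dose and the sample size are unaffected.

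**What to change.** Define the poststudy LVEF, BNP and NYHA value at one fixed time from randomization, with a stated window, for every randomized patient whatever the titration status. The 6-month horizon used in Sample Size Calculation is one natural example. Take the values from the chart reviews already planned, base the between-arm tests on them, and report how many patients per arm have one. Label values anchored to titration completion as descriptive.

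Two pairs of statements must also be reconciled: a follow-up within 3 months of completion against the 3-month follow-up in Table 1, and control-arm tests done as required against the Table 1 ticks.

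The cost is amendment wording and a chart-review window. Titration, sample size, alpha and power do not change, and no extra echocardiograms need be required. The downside is some imperfectly timed or missing values, especially among the 76 patients already enrolled by February 24, 2020. Control LVEF is the most exposed, because in Scenario A its median follow-up falls at 9 to 10 months. The window should be chosen with that in mind and without looking at results by arm.
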